### Adverse Event Severity and Relationship to Study Drug

The investigators will rate the severity of each AE according to the National Cancer Institute (NCI) Common Terminology Criteria for Adverse Events (CTCAE), version 5.0. If a reported AE increases in

severity, the initial AE should be given an outcome date and a new AE must be reported to reflect the change in severity. The dates on the AEs cannot overlap. For all reported SAEs that increase in severity, the supplemental eCRFs also need to be updated to reflect any changes due to the increase in severity.

For AEs not captured by the NCI CTCAE, the following should be used:

|                |                                                                                                                             |
|----------------|-----------------------------------------------------------------------------------------------------------------------------|
| Grade 1 | The AE is transient and easily tolerated by the subject (mild).                                                             |
| Grade 2 | The AE causes the subject discomfort and interrupts the subject's usual activities (moderate).                              |
| Grade 3 | The AE causes considerable interference with the subject's usual activities and may be incapacitating (moderate to severe). |
| Grade 4 | The AE is life-threatening and requires urgent intervention (severe).                                                       |
| Grade 5 | The AE resulted in death of the subject (severe).                                                                           |

The investigator will use the following definitions to assess the relationship of the AE to the use of study drug:

|                                  |                                                                                                                                                                                                                          |
|----------------------------------|--------------------------------------------------------------------------------------------------------------------------------------------------------------------------------------------------------------------------|
| Reasonable Possibility    | After consideration of factors including timing of the event, biologic plausibility, clinical judgment, and potential alternative causes, there is sufficient evidence (information) to suggest a causal relationship.   |
| No Reasonable Possibility | After consideration of factors including timing of the event, biologic plausibility, clinical judgment, and potential alternative causes, there is insufficient evidence (information) to suggest a causal relationship. |

## Pregnancy

While not an AE, pregnancy in a study subject must be reported to AbbVie within 24 hours after the site becomes aware of the pregnancy. Subjects who become pregnant during the study must be discontinued (Section 5.5). If a pregnancy occurs in a study subject or in the partner of a study subject, information regarding the pregnancy and the outcome will be collected.

In the event of pregnancy occurring in a subject's partner during the study, written informed consent from the partner must be obtained prior to collection of any such information. AbbVie will provide a separate consent form for this purpose. Pregnancy in a subject's partners will be collected from the date of the first dose through 90 days following the last dose of study drug.

The pregnancy outcome of an elective or spontaneous abortion, stillbirth or congenital anomaly is considered a SAE and must be reported to AbbVie within 24 hours after the site becomes aware of the event.

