| 4-week (5-dose) IV infusion with a 4-week recovery period in Sprague-Dawley rat (CrI:CD®(SD))
aged 10 weeks at initiation of dosing | 
 
• 10/sex (main)
 
• 5/sex for recovery (control, mid, high)
 
 | 0, 10, 30, 60, 100  | Effects observed in 
 
• Pancreas – single-cell necrosis, increased amylase and lipase
 
• Liver – increased ALT/AST, multinucleated hepatocytes
 
• Bone marrow – decreased cellularity, red and white blood
 
• Gastrointestinal tract – epithelial degeneration and regeneration
 
• Lymphoid system – lymphoid cell depletion and/or necrosis in multiple lymphoid tissues
 
• Testes – degeneration/atrophy of seminiferous tubules
 
• Multiple other tissues – single-cell necrosis
 
                                                                                                                                                                                                          |
| 4-week (5-dose) IV infusion with a 4-week recovery period in beagle dog
aged 8-8.5 months at initiation of dosing                   | 
 
• 4/sex (main)
 
• 2/sex for recovery (control, mid, high)
 
  | 0, 1, 3, 10         | Mortality at 10 mg/kg after 1 or 2 doses (days 3–10) attributed to on-target effects in gastrointestinal tract, pancreas, and bone marrow
Effects observed in 
 
• Pancreas – single-cell necrosis, acinar atrophy/necrosis, and increased amylase and lipase
 
• Liver – profound increases in ALT and AST, hepatocyte necrosis, bile cholestasis
 
• Bone marrow – decreased cellularity, red and white blood
 
• Gastrointestinal tract – necrosis and/or hemorrhage
 
• Lymphoid system – decreased circulating lymphocytes, lymphoid cell necrosis in multiple lymphoid tissues
 
• Testes – degeneration/atrophy of seminiferous tubules
 
• Multiple other tissues – single-cell necrosis
 
 |

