## 4 INVESTIGATIONAL PLAN

### 4.1 Overall Study Design and Plan

---

This is a Phase 1, first-in-human, open-label, dose escalation and dose expansion study evaluating ABBV-467 in subjects with R/R MM and R/R AML; the schematic of the study is shown in [Figure 1](#). Further details regarding study procedures are located in the Operations Manual. See [Section 5](#) for information regarding eligibility criteria. Dosing will be weekly, on a 28-day cycle, though alternative

dosing frequencies may be studied if supported by the totality of safety, efficacy, PK, and/or pharmacodynamic (PD) data.

Subjects will continue ABBV-467 therapy until disease progression, unacceptable toxicity, or withdrawal of consent. No subject will receive ABBV-467 for longer than 24 months within the context of this study.

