### Contraception

- ✓ 27. For all females of child-bearing potential; a **negative serum pregnancy test** at the Screening Visit and a negative urine pregnancy test at baseline prior to the first dose of study drug.
- ✓ 28. Female subjects of childbearing potential must practice at least 1 protocol-specified **method of birth control**, that is effective from C1D1 through at least 185 days after the last dose of study drug (refer to Section 5.2).
- ✓ 29. Female must not be **pregnant, breastfeeding (even if breastfeeding is interrupted), or considering becoming pregnant** during the study or for approximately 185 days after the last dose of study drug.
- ✓ 30. **If male**, and subject is **sexually active with female partner(s) of childbearing potential**, he must agree, from C1D1 through 95 days after the last dose of study drug, to practice the protocol-specified contraception (refer to Section 5.2).
- ✓ 31. Male must not be considering **fathering a child or donating sperm** during the study or for approximately 95 days after the last dose of study drug.

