### Contraception Requirements for Males

Male subjects who are sexually active with a female partner of childbearing potential, must agree **to use condoms, even if the male subject has undergone a successful vasectomy**, from C1D1 through at least 95 days after the last dose of study drug:

- His female partner(s) must also use at least 1 of the following methods of birth control:
  - Combined (estrogen and progestogen containing) hormonal birth control (oral, intravaginal, transdermal, injectable) associated with inhibition of ovulation initiated at least 30 days prior to study Baseline Day 1.
  - Progestogen-only hormonal birth control (oral, injectable, implantable) associated with inhibition of ovulation initiated at least 1 month prior to study Baseline Day 1.
  - Bilateral tubal occlusion/ligation (can be via hysteroscopy, provided a hysterosalpingogram confirms success of the procedure).
  - IUD.
  - IUS.

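### Partner pregnancies are collected only through 90 days after the last dose, 5 days short of the protocol's own 95-day male contraception window

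*Protocol*

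**What the plan says.** Section 6.1 (Pregnancy) sets a period for pregnancies in a subject's partner: these "will be collected from the date of the first dose through 90 days following the last dose of study drug".

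The male precaution period is set in three other places:

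- Section 5.1, criterion 30: a sexually active male with a partner of childbearing potential must use the specified contraception "from C1D1 through 95 days after the last dose of study drug".
- Section 5.1, criterion 31: he must not be considering fathering a child or donating sperm during the study or "for approximately 95 days after the last dose of study drug".
- Section 5.2 (Contraception Requirements for Males): condoms are required from C1D1 "through at least 95 days after the last dose of study drug", and the partner must also use a listed method.

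Two further sentences in Section 6.1 carry no day limit. One says that, if a pregnancy occurs in a subject or a partner, "information regarding the pregnancy and the outcome will be collected". The other says that a pregnancy outcome of "elective or spontaneous abortion, stillbirth or congenital anomaly is considered a SAE", to be reported within 24 hours of the site learning of it. A separate consent form is to be provided for partners; it is not among the documents shown.

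**The concern.** The contraception window is the sponsor's own statement of how long conception should be avoided after a man's last dose. The collection window for partner pregnancies exists to capture the cases in which that precaution fails, so it should be at least as long. Here it ends earlier. In a first-in-human trial each partner pregnancy is scarce safety information. A site that follows the 90-day sentence could properly leave one unrecorded although the subject was still inside the precaution period. What is at stake is the completeness of a small safety record, not any statistical result.

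**Working it through.** No sample size, power or error rate is involved. The check sets the stated windows side by side.

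| Rule | Where | Start | End |
|---|---|---|---|
| Partner pregnancy collected | Section 6.1, Pregnancy | first dose | last dose + 90 days |
| Male contraception | Section 5.1, criterion 30 | C1D1 | last dose + 95 days |
| Male contraception | Section 5.2 | C1D1 | last dose + at least 95 days |
| No fathering or sperm donation | Section 5.1, criterion 31 | during the study | last dose + approximately 95 days |

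1. **Anchors.** The first dose is given on C1D1, and every end date is counted from the last dose of study drug. The windows therefore compare day for day.
2. **Difference.** 95 − 90 = 5 days, namely days 91 to 95 after the last dose. Since Section 5.2 makes 95 days a minimum, 5 days is the least shortfall against that section.
3. **Which figures are firm.** Criterion 30 and Section 5.2 are exact or a minimum. Criterion 31 is approximate and does not by itself contradict 90 days, so the point rests on the first two.
4. **What the 90 days refers to.** Section 6.1 does not say whether a pregnancy is dated by conception or by detection. The 5-day figure assumes conception, which is what the contraception window governs. If detection were meant, a pregnancy conceived before day 90 but recognised afterwards would also fall outside, and the shortfall would be larger. The documents do not allow that to be quantified.
5. **After the change.** With collection through at least 95 days, the gap to criterion 30 is 95 − 95 = 0 days.
6. **Scheduled contacts.** Operations Manual Section 2.2 has a visit 30 days (± 7) after the last dose, then contacts every 3 months after that visit (± 7 days). Taking 3 months as about 90 days, the first such contact falls near day 30 + 90 = 120, and no earlier than about day 23 + 90 − 7 = 106. No scheduled contact falls on days 91 to 95. The 3-monthly contacts list disease status, survival and subsequent therapy, and none asks about partner pregnancy.

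**The case against.** The strongest case against acting is that one window governs prevention and the other data collection, and nothing in the protocol says they must match. There is also little operational effect: by step 6 above, the change only decides whether a volunteered pregnancy dated to those five days must be recorded. Condoms plus a partner method make such a pregnancy unlikely. All of this limits the size of the point. It does not remove it: the protocol fixes both numbers, they do not fit together, and no reason is given for the shorter one.

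Three stronger readings are tempting, and the documents do not support them.

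- **That Section 6.1 contradicts itself.** A reader might set the two sentences without a day limit against the 90-day sentence. But the general sentence says what is collected when a pregnancy occurs, and the 90-day sentence in the next paragraph says when for partners; the specific qualifies the general. The SAE sentence classifies outcomes and sets reporting speed. It rightly has no day limit, because a pregnancy that began within the window can end months later.
- **That the animal findings make the gap serious.** Supplementary Table S7 lists "degeneration/atrophy of seminiferous tubules" in both rats and dogs. Its footnote calls all findings dose dependent and partially to fully reversible, and the table reports nothing about harm to a partner's pregnancy.
- **That the five days can be scaled as a share of the observation window.** Such a share measures calendar time. It says nothing about the number of pregnancies or the risk to them.

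**Conclusion.** The point holds as a minor misalignment. Section 6.1 ends collection of partner pregnancies 5 days before the male contraception window in criterion 30 closes, and at least 5 days before the one in Section 5.2. A partner pregnancy arising on days 91 to 95 therefore need not be collected. The conclusion rests on two readings: that the 90-day sentence governs partner pregnancies, and that its 90 days is counted to conception. The effect is limited to safety data collection. The recommended Phase 2 dose, the DLT assessment, the pharmacokinetic and efficacy endpoints, and every planned analysis are untouched.

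**What to change.** In the Section 6.1 sentence on partners, change 90 days to at least 95 days, and preferably state that the window refers to the estimated date of conception. Possible wording: *Partner pregnancies with an estimated conception date from the first dose until at least 95 days after the last dose are to be collected.* The conception rule is new to the protocol, but it settles how a pregnancy reported later is to be dated. Leave the SAE rule for pregnancy outcomes and the rule for pregnancy in study subjects as they are.

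The cost is one sentence, with no new visit or test. Section 8.1 requires ethics committee approval before any amendment takes effect, so the change belongs in the next planned amendment and does not justify one of its own. The partner consent form needs the same edit only if it states 90 days.

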## 6.2 Toxicity Management

---

### ABBV-467 Dosing Modifications for Toxicity

After Cycle 1, doses of ABBV-467 can be delayed up to 1 day due to toxicity; delays any longer than 1 day should result in the dose being skipped. If the Day 8 dose is skipped or delayed, the subject should resume dosing on Day 15 (provided that any toxicities requiring dose delay or interruption have resolved), and so on. If the Day 22 dose is skipped or delayed, the subject should complete the 28-day cycle on schedule and resume dosing at the start of the next cycle (provided that any toxicities requiring dose delay or interruption have resolved). If the ABBV-467 Day 1 dose of any cycle is delayed, then the start of the cycle should be delayed until the next dose of ABBV-467 is administered.

For any subject who experiences Grade 3/4 toxicity which is attributed to ABBV-467, the dose will be held until the toxicity resolves to Grade 1 or lower, or to baseline if the toxicity was > Grade 1 at the time of study entry. Upon toxicity resolution, the subject may restart study drug at 75% of that subject's starting dose (i.e., a 25% dose reduction). Following similar guidelines, subsequent dose reductions to 50% of the starting dose, and then a 25% of the starting dose, may be implemented. Dose reductions below 25% of the subject's starting dose are not allowed.

In addition, subjects with AML who experience CR or PR with hematologic recovery after receiving ABBV-467 and then experience Grade > 3 hematologic AE should undergo a bone marrow evaluation to determine if cytopenias are due to drug toxicity or recurrent disease.

Study drug interruptions for events that are considered not related to the study drug (e.g., underlying cancer, planned surgical procedures or acute viral illnesses), should not necessitate a dose reduction. The timing of dose resumption should be at the discretion of the Investigator.

Subjects experiencing a delay longer than 28 days due to an AE(s) related to study treatment should be permanently discontinued from study treatment. Subjects experiencing a delay longer than 28 days unrelated to study treatment must be discussed with the AbbVie TA MD or designee.

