**Table 2. Proposed Dose Levels**

| Dose Level   | 1    | 2    | 3    |  |  |  |  |  |  |  |  |
|--------------|------|------|------|--|--|--|--|--|--|--|--|
| Dose (mg/kg) | 0.16 | 0.32 | 0.53 |  |  |  |  |  |  |  |  |

Throughout all parts of the study, ABBV-467 will be administered with an abbreviated dose ramp-up, in which 50% of the target dose will be administered on Cycle 1 Day 1 (C1D1), and full target dose thereafter (weekly until disease progression, unacceptable toxicity, or withdrawal of consent).

For each dose level, the second subject will not be dosed until at least 48 hours have elapsed since the initial dose for the first subject at that dose level.

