## 5.7 Study Drug

---

ABBV-467, manufactured by AbbVie, should be administered as an intravenous (IV) infusion via a central venous catheter (CVC) (e.g., peripherally inserted central catheter line, port line) once weekly (QW), for each 28-day cycle over at least a 30-minute period beginning on C1D1. For any particular dose level below 1.4 mg/kg, a peripheral IV may be used if/when CVC placement is unavailable or contraindicated (CVC use is mandatory for any dose 1.4 mg/kg or higher due to possibly increased risk of adverse local/skin reactions). Subjects receiving study drug via peripheral IV should be monitored closely for extravasation and/or local irritation (which, if observed, should be reported to Sponsor). Doses will be determined by dose-escalation decision rules; the starting dose is 0.16 mg/kg. ABBV-467 can be administered with or without food. The first dose of ABBV-467 on C1D1 will be administered at half the targeted dose for a given subject; subsequent doses will be administered at the full target dose. After completion of Cycle 1, ABBV-467 doses may be delayed for up to 1 day due to scheduling conflicts; delays longer than 1 day should result in the dose being skipped. If there is a less than 10% weight change from weight on C1D1, no dose adjustment is necessary.

During preparation of the dose for infusion and during infusion, the solution must be protected from light. As the phototoxic potential of ABBV-467 is unknown, subjects will be advised to limit sunlight exposure during participation in the trial.

Study drug will be administered at the site with appropriate medical support available to manage infusion reactions if they occur. The study site personnel will document compliance.

AbbVie will provide instructions for drug preparation. AbbVie will not supply drugs other than ABBV-467.

Study drug information is presented in [Table 3](#).

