### AML-Specific Dose Modifications for Drug-Related Hematologic Toxicities

If a subject with AML experiences hematologic toxicity during the study, the dose of ABBV-467 should be modified as indicated in [Table 4](#).

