## Tumor Lysis Syndrome

Subjects with MM with high tumor burden (e.g., high bone marrow plasma cell infiltration, plasma cell leukemia, or bulky plasmacytomas), rapidly increasing M-protein or light chains or high proliferative activity, plasmablastic morphology, or compromised renal function ( $CrCl < 50$  mL/minute) may be at higher risk of developing TLS. There is a potential risk for TLS in subjects with AML, especially in those with elevated leukocyte count, circulating blasts, elevated pretreatment lactate dehydrogenase levels, renal dysfunction, and dehydration. To mitigate the risk for TLS all subjects enrolled into the study will need TLS prophylaxis and monitoring. For subjects at higher risk for TLS, additional mitigation measures with more intensive laboratory monitoring and intervention should be implemented. Prophylactic reductions of potassium, inorganic phosphorus or uric acid above normal range are recommended prior to beginning study treatment and to be continued based on the ongoing risk of TLS. Please reference [Appendix F](#) for additional information on the evidence of TLS and [Appendix G](#) for initial management of electrolyte abnormalities and prevention of TLS.

During dose escalation, each subject should be hospitalized the night prior to C1D1 for hydration, treatment with uric acid-reducing agents, and monitoring. Tumor lysis syndrome laboratories will be obtained at 3 different time points: immediately prior to the first dose, 6 to 8 hours after the first dose, and approximately 24 hours after the first dose (on C1D2).

The subject may be discharged once the laboratory results on C1D2 are reviewed (approximately 24 hours after first dose) and confirm the absence of TLS. If discharged since first dose, subjects will be re-hospitalized the night prior to C1D8 for hydration, treatment with uric acid-reducing agents, and monitoring.

Tumor lysis syndrome prophylaxis and management for the second dose of ABBV-467 will be managed in the same manner as the first dose described above. Subjects who experience clinical or laboratory TLS, or other significant toxicity following the first or second dose of ABBV-467 should discuss the safety monitoring plan for subsequent doses of ABBV-467 with the AbbVie TA MD.

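### The general restart ladder in Protocol Section 6.2 is not tied to the dose last received, so after a Grade 3/4 event on the Cycle 1 Day 1 half dose it permits a restart at 1.5 times that dose while calling it a 25% reduction

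*Protocol*

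**What the plan says.** Section 6.2 (ABBV-467 Dosing Modifications for Toxicity) holds the drug for any subject with a Grade 3/4 toxicity attributed to ABBV-467 until it falls to Grade 1 or baseline. It then says: "Upon toxicity resolution, the subject may restart study drug at 75% of that subject's starting dose (i.e., a 25% dose reduction". The lower steps and the floor follow: "Following similar guidelines, subsequent dose reductions to 50% of the starting dose, and then a 25% of the starting dose, may be implemented", and "Dose reductions below 25% of the subject's starting dose are not allowed". Each step is expressed against the starting dose and none against the dose last given. The rule is not restricted to events after Cycle 1 or after a full dose.

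The ramp-up is set in Section 4.1 (text under Table 2): "50% of the target dose will be administered on Cycle 1 Day 1 (C1D1), and full target dose thereafter". Section 5.7 repeats it: "The first dose of ABBV-467 on C1D1 will be administered at half the targeted dose for a given subject". Section 5.7 also states, for the study as a whole, that "the starting dose is 0.16 mg/kg". That figure is the full target of dose level 1, not the 0.08 mg/kg given first at that level.

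Several toxicities have their own rules in Section 6.2:

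- **Hepatic and pancreatic:** where a restart at reduced dose is allowed, it must be at least 33% under the preceding dose.
- **Cardiac and infusion/allergic:** the sponsor's medical director is consulted before dosing resumes; no dose is fixed.
- **Tumor lysis syndrome (TLS):** dosing stops until resolution.
- **AML hematologic:** "If a subject with AML experiences hematologic toxicity during the study, the dose of ABBV-467 should be modified as indicated in" Table 4, which works by delay or by dropping Day 22.

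**The concern.** The ladder assumes that the subject was on full dose when the toxicity occurred. For roughly the first week this is not so, because only the half dose has been given. A Grade 3/4 event in that week that has no rule of its own falls to the general ladder, and a step labelled as a reduction then exceeds the dose that has just proved toxic. Gastrointestinal toxicity is one example; hematologic toxicity in a myeloma subject is another, since Table 4 covers AML only.

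This is a first-in-human trial, and what is at stake is the dose given to an individual subject who has already had a severe drug-related event. The hepatic and pancreatic rules already tie the restart to the preceding dose. The general rule lacks that link.

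**Working it through.** **Inputs.** Let T be the target dose. Levels 1 to 3 are T = 0.16, 0.32 and 0.53 mg/kg (Table 2). The C1D1 dose is 0.5T (Sections 4.1 and 5.7). The ladder is 75%, 50% and 25% of the starting dose (Section 6.2).

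**The plan's own figure.** Take the starting dose as T and an event on full dose: 0.75T/T = 0.75, a 25% reduction. The stated figure is reproduced.

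**Event after C1D1, before the first full dose.** The dose last received is 0.5T.

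- 75% step: 0.75T/0.5T = 1.5
- 50% step: 0.50T/0.5T = 1.0
- 25% step: 0.25T/0.5T = 0.5

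| Level | T (mg/kg) | C1D1 dose | 75% step | 50% step | 25% step |
|---|---|---|---|---|---|
| 1 | 0.16 | 0.08 | 0.12 | 0.08 | 0.04 |
| 2 | 0.32 | 0.16 | 0.24 | 0.16 | 0.08 |
| 3 | 0.53 | 0.265 | 0.3975 | 0.265 | 0.1325 |

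One of the three permitted steps is a real reduction.

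**Comparison with the organ-specific rule.** A reduction of at least 33% from the same half dose gives at most 0.67 × 0.5T = 0.335T. At level 1 this is 0.67 × 0.08 = 0.0536 mg/kg, against 0.12 mg/kg under the general rule.

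**The other reading of the term.** If a subject's starting dose means the dose actually given on C1D1, the first step is 0.75 × 0.5T = 0.375T. After a half-dose event that is a true 25% reduction. After a full-dose event it is 1 − 0.375 = 62.5%, so the 25% label fails there. Neither reading makes the label true of the dose last received in both situations.

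**Do other provisions limit the restart dose?**

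- Section 6.2 (Tumor Lysis Syndrome): subjects with TLS or "other significant toxicity following the first or second dose of ABBV-467 should discuss the safety monitoring plan for subsequent doses" with the medical director. This adds review, not a dose limit.
- Section 6.3: a dose missed because of toxicity that the disease does not explain counts as a DLT. This informs the cohort decision, not this subject's restart dose.
- Operations Manual Section 3.15: the investigator contacts the sponsor about dose reductions for significant laboratory values. No dose is given.
- Section 5.5: withdrawal is possible. Section 6.2 makes it mandatory if a treatment-related delay exceeds 28 days. A toxicity that resolves sooner can still go to the ladder.

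**The case against.** **The term is undefined.** The 1.5 ratio needs *starting dose* to mean the target. Section 5.7 uses the phrase for the trial's first dose level, not for a subject, and the bracketed 25% suggests that the authors had a subject on full dose in mind. This stands as a caveat: for half-dose events the text may be called unclear rather than a deliberate authorisation. The target reading is still the natural one, because only then does the 25% label hold for full-dose events, and the term needs fixing on either reading.

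**The label has a true sense.** Against the full dose due next, 75% of target is 25% lower. That is correct, but it does not describe the change from the dose that caused the event.

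**The case is small and reviewed.** The wording is permissive, the window is about a week, several toxicities have their own rules, and Section 6.2 calls for a discussion aimed at toxicity after the first or second dose. All of this stands and limits how often the problem can arise. None of it sets a maximum restart dose.

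**A cap on every restart would do harm.** A reader might infer that any restart after a drug-related Grade 3/4 event should be below the last dose. The protocol does not support that. Table 4 manages AML cytopenias by delay or schedule without cutting the dose, and infusion or allergic reactions are left to discussion with the medical director. A universal cap would contradict both, so the remedy must be confined to the general ladder.

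**Conclusion.** The point holds within limits. On the natural reading, the general ladder permits a restart at 1.5 times the causative dose after a drug-related Grade 3/4 event that follows the C1D1 half dose and precedes the first full dose. It describes this as a 25% reduction, and its second step repeats the causative dose. The result rests on two conditions: *starting dose* means the assigned target, and the toxicity is outside the hepatic, pancreatic, cardiac, infusion/allergic, TLS and AML-hematologic rules.

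Two stronger readings are not supported. A reader might infer that the protocol requires the higher dose; it only allows it. A reader might also infer that the ladder is wrong in general; for events on full dose handled by the ladder it works as labelled. No sample size, endpoint or operating characteristic is affected. It is a narrow flaw in a stated safety rule and should be corrected in an amendment.

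**What to change.** In the general dosing-modification text of Section 6.2, replace *starting dose* with *assigned target dose* in all four places, and add:

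> When study drug is restarted under this general ladder, the restart dose must be lower than the dose last received before the toxicity; ladder steps at or above that dose are skipped. This does not alter the toxicity-specific rules elsewhere in Section 6.2, including Table 4 and the infusion/allergic reaction rules.

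After a C1D1 event this leaves the 25% step: 0.04, 0.08 or 0.1325 mg/kg at levels 1 to 3. If that is too severe, the sponsor can write in a step at 37.5% of target (0.06, 0.12 or about 0.199 mg/kg), a true 25% reduction from the half dose.

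The cap should apply to every restart under the general ladder, not only the first. Without it, a second event at 37.5% could lead up to the 50% step (0.50/0.375 = 1.33). A subject cut to 67% of target under the hepatic or pancreatic rule who later has a different Grade 3/4 event could go up to 75% (0.75/0.67 = 1.12), if 75% is taken as the first general step.

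Events on full dose handled by the general ladder keep the sequence 100, 75, 50, 25%. The change needs one term replaced and a short addition, with no new data or procedures. The downside is clinical: after a C1D1 event one step remains instead of three (two with a 37.5% step), so a subject may stop treatment sooner.
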